### Study population and setting

Study populations will be adults, unemployed and economically inactive^2^ enrolled in community treatment for AUD, OUD or another drug use disorder. The minimum total target sample will be 832 participants. The plan is to include seven clinical recruitment sites in Birmingham, Blackpool, Brighton and Hove, Derbyshire, London Borough of Haringey, Sheffield and Staffordshire. Each site will be a NHS, not-for-profit, or private organisation providing community/outpatient treatment for alcohol and drug dependence. According to the treatment capacity of each site, two or more Employment specialists (ES) will deliver IPS.

### Participant inclusion criteria

Patients will be eligible to take part if they meet the following inclusion criteria:
Aged 18–65 yearsEnrolled in treatment for drug or alcohol use disorder for at least 14 days with current diagnosis of a specified drug and/or alcohol use disorderUnemployed or inactive at study screening visit for at least 6 months with a declared wish to obtain open job market employmentAble to attend the community addiction clinic as required in the protocolAble to communicate (verbal and written English) at a level required to engage with a psychosocial interventionAble to provide a personal National Insurance Number (NINO) to facilitate data linkage^3^

### Participant exclusion criteria

Otherwise eligible patients will not be able to join the study if one or more of the following exclusion criteria are met:
Currently receiving detoxification treatment for drug or alcohol withdrawalClinically significant (or otherwise uncontrolled) severe mental health, intellectual disability, organic brain disease or dementia, or physical disability that is judged by the local clinical lead to prevent the person accepting IPSSuicide planning (past month) or suicide attempt (past 6 months)Current legal proceedings which are likely to result in imprisonmentEnrolment in an IPS trial, or in the past 6 monthsPreviously enrolled in the IPS-AD study

### Procedure

All keyworkers and ES will complete National Institute for Health Research’s Good Clinical Practice (GCP) training. Potential participants will be referred to an ES in the clinical team to discuss the study. The King’s College London Clinical Trials Unit will programme and independently manage the study randomisation system on a secure website. Immediately after securing informed consent (IPS-AD Participant Information Sheet (PIS) and Participant Consent Form (PCF) is available from the corresponding author on request) and completion of baseline study questionnaires, the ES will access the randomisation website to assign the participant to the intervention or control condition. Group allocation (ratio 1:1) will be done using block randomisation (with varying block size) stratified by site, clinical diagnosis (AUD, OUD, other drug use disorder) and work history (1 month or less versus more than 1 month of paid employment in the last 5 years).

The randomisation system will immediately confirm the participant’s allocation to IPS or TAU by email. The ES will then inform the participant and their keyworker. Participants assigned to TAU will be given an information pack containing details of standard employment support services available locally and will have no further contact with the ES. It will not be feasible to blind clinicians to trial condition allocation. Enrolment in TAU will be ongoing after the trial according to patient preference and local policy.

### IPS intervention principles and delivery

IPS will be offered as an individual (one-to-one) intervention for 9 months with up to four additional months of in-work support if competitive employment is attained. IPS will be provided without restriction due to job readiness, work history, qualifications and homelessness status. In weekly sessions in the first month, the ES will: (1) discuss opportunities to work and will give advice on welfare benefits, including the availability of in-work benefits; (2) develop a vocational profile of the participant’s skills, experience and employment preferences; (3) help the participant to write or update their curriculum vitae/resumé; and (4) help the participant to implement a rapid job search. As appropriate, the ES will contact local employers and help the participant to complete job applications and prepare for interviews. The ES will seek to develop relationships with local employers and discuss opportunities to tailor work for people recovering from alcohol and drug dependence.

After the first month, IPS sessions will be scheduled approximately fortnightly, with additional phone and email contact provided as needed. Once the participant starts work, the ES will offer in-work support. This support will be approximately weekly contacts in the first month, then fortnightly. The ES will discuss how the participant is adapting to their new job; assist with any referral for medical treatment; and, with consent, seek to discuss job-flexibility issues with the employer (e.g. adjusting shift patterns to enable the participant to collect treatment medication from a retail pharmacy).

### Standard employment support

Vocationally, participants randomised to the TAU control group will receive standard employment support only. For participants receiving Jobseeker’s Allowance (JSA) or Universal Credit (UC) with all work-related requirements, TAU will usually involve support from Jobcentre Plus (JCP) and/or the Work and Health Programme (WHP). TAU may also include standard employment support provided by the addiction-treatment programme or other local services.^4^

### IPS training for ES

Training for ES will consist of a continuing professional development (CPD) accredited 2-day course facilitated by the Centre for Mental Health (CMH) and a 12-week online ES practitioner skills course provided by the USA IPS Employment Center. IPS-AD recruitment sites will be encouraged to look for CPD opportunities for the ES team, including forging links with the local IPS Centre of Excellence and with IPS Grow (the latter an IPS capacity building network in the NHS and mental health services with support funding from NHS England and the DWP).

### IPS fidelity

To help develop and maintain IPS fidelity, IPS-AD will use the 25-item Individual Placement and Support Fidelity Scale (IPS-25) [20]. The IPS-25 was adapted to the UK context by the CMH [21] and has three sections: staffing, organisation and services. Independent reviewers score items on the scale using a 5-point response format (1 = no implementation; 5 = full implementation), with intermediate numbers representing progressively greater degrees of implementation. The maximum score is 125 points. During the study, the CMH will co-ordinate all fidelity reviewers with another organisation called Social Finance (SF). CMH and SF raters will complete the IPS-25 with access to multiple sources of information, including interviews with study participants, ES and managers, as well as reviewing case records and observing the day-to-day practice of the IPS and clinical teams. From the start of the study, there will be planned fidelity reviews at each site at 5–7 months and 15–18 months. CMH and SF will provide each site with a detailed report of their IPS-25 score and will provide advice on how this can be improved.

### Realist process evaluation

RAND Europe and the CMH will conduct the IPS-AD process evaluation. Theory-driven and following realist principles, this will investigate IPS and clinical practice and answer questions of the characteristics of patients and IPS exposure that are associated with competitive employment outcomes. An initial focus will be on any obstacles encountered during the set-up of IPS in each site and how IPS is integrated into routine procedures. In each site, RAND Europe and CMH researchers will conduct personal interviews (each audio-recorded with permission) with a random sample of participants allocated to IPS and TAU as well as a convenience sample of ES, treatment service commissioners, managers, keyworkers, local JCP staff and employers.

### Primary outcome measure

The primary outcome of the study is competitive employment status. This outcome will be met if the participant obtains at least 7 h (i.e. 1 day) of employment in the open competitive job market at any time following randomisation to the end of an 18-month follow-up. This outcome measure has been commonly used in IPS efficacy studies and meta-analysis. We will determine this outcome by linking participant-level information with the Department for Work and Pensions’ (DWP) Work and Pensions Longitudinal Study (WPLS) database.

### Secondary outcome measures

#### Vocational

IPS-AD includes the following secondary vocational outcome measures:
Total time (days) in competitive employment (and corresponding National Insurance contributions (NIC) and tax paid)Time (days) from randomisation to first competitive employmentNumber of competitive job appointmentsJob tenure (length of longest held competitive employment)Sustained employment (tenure in a single appointment for at least 13 weeks)^5^Job search self-efficacy

The time and count-based vocational outcomes will be determined from extracts of the WPLS database using the dates of starting and stopping competitive employment. NIC and tax records from randomisation to the end of follow-up will be determined using HMRC’s Real Time Information system (RTI).

Job search self-efficacy (for a mediation analysis of outcome) will be assessed by the six-item Job Search Self-Efficacy: Behaviour scale (JSSE-B) [22]. The JSSE-B includes measures of confidence in making a good impression, making a good application, and using friends and contacts to discover vacancies. The JSSE-B has been shown to predict job search behaviour. Site clinicians will complete the JSSE-B during personal interviews at baseline, 6 months, 12 months and 18 months or at treatment exit if earlier (the latter if feasible).

#### Alcohol and drug dependence treatment-related

For the secondary outcomes and economic analyses, the following alcohol and drug dependence treatment-related outcomes will be included:
Alcohol consumption, drug use, drug injectingDSM-5 AUD, OUD and other drug use disorder remission statusTotal time enrolled in alcohol and drug use disorder treatmentNumber of AUD, OUD and other drug use disorder treatment episodesTreatment status at end of follow-up (enrolled, left successfully, left unsuccessfully, deceased)

Alcohol and drug use (recall: past 28 days) will be self-reported to site clinicians using the Treatment Outcomes Profile (TOP) [23]. The TOP is the English national outcomes monitoring instrument for publicly funded treatment services for drug and alcohol dependence. TOP data is uploaded to the National Drug Treatment Monitoring System (NDTMS). The TOP uses a structured, calendar-prompt, ‘timeline follow-back’ procedure [24] to maximise accuracy of drug and alcohol use reporting. The TOP will be administered by site clinicians as a structured personal interview at baseline, 6 months, 12 months,18 months and exit.

DSM-5 remission status will be assessed by personal interview by site clinicians at baseline, 6 months, 12 months and 18 months using the Structured Clinical Interview for DSM-5 (clinician version; SCID-5-CV) [25]. This has a checklist of 11 symptoms (each coded ‘present’ or ‘absent’) to diagnose disorder presence and severity (no symptoms = disorder not present; 1–3 symptoms = mild; 4–5 symptoms = moderate; ≥ 6 symptoms = severe). We will use the American Psychiatric Association’s definition for AUD and OUD remission (i.e. zero criteria except craving and using the ‘on maintenance therapy’ specifier as appropriate and not including tolerance and withdrawal item if the patient is adherent to their prescription).

NDTMS records will be used to determine each participant’s total time in treatment in the community and in prison, as well as the number of treatment episodes and status at the end of follow-up. For data modelling, we will record TOP and treatment exposure data for 18 months prior to randomisation for those members of the cohort with a history of prior treatment for alcohol and drug dependence.

#### Social and health

For the economic analysis, the following social and economic outcomes will be included:
Welfare payments (i.e. Job Seeker’s Allowance (JSA); Income Support (IS) Employment and Support Allowance (ESA); Universal Credit (UC); Housing Benefit (HB) and Tax Credits (TC))NHS hospital attendances and admissions (A&E, outpatient and inpatient)EuroQol 5-dimension, 5-level health survey (EQ-5D-5 L)MortalityConvictionsPrison sentences

JSA, IS, ESA, UC and HB welfare payments will be determined from the dates of starting and stopping receipt of each benefit type, or changes to levels of payment of each type, recorded in the following DWP databases: National Benefits Database (JSA, IS and ESA); and Universal Credit Official Statistics (UC), Housing Benefit Extract (HB). Tax Credit spells and amounts will be determined by use of HMRC’s General Matching System (GMS).

Hospital care will be recorded by Hospital Episode Statistics (HES; PHE is the data controller). The Office for National Statistics’ (ONS) register of births and deaths will record mortality.

Convictions and prison sentences will be recorded from extracts from the Police National Computer (PNC) and the National Offender Management Information System (p-NOMIS), respectively (both operated by the Ministry of Justice).

The EQ-5D-5 L [26] is a brief generic scale recording mobility, self-care, usual activities, pain/discomfort, anxiety/depression, with a 0 to 100-point vertical visual analogue scale (VAS) measuring overall health status. Site clinicians will complete this measure during personal interviews at baseline, 6 months, 12 months and 18 months and exit. HES, DWP and HMRC welfare payments, PNC and p-NOMIS data will be recorded from randomisation to the end of follow-up. For data modelling, we will also record these outcomes for 18 months prior to randomisation.

The schedule of enrolment, allocation, interventions and assessments is summarised in Table 1.

**Table 1 Tab1:**
[figure not shown]
Schedule of enrolment, allocation, interventions and assessments

*AE form* adverse events form, *AUD* alcohol use disorder, *EQ-5D-5 L* EuroQol five-level health status, *ES* employment specialist, *FSS* Universal Credit Full Service System (Department for Work and Pensions), *GMS* General Matching System (Her Majesty’s Revenue and Customs), *HES* Hospital Episode Statistics (Public Health England), *IPS* Individual Placement and Support (the experimental intervention), *JSSE-B* Job Search Self-efficacy scale, *KW* treatment service keyworker, *LMS* Labour Market System, Department for Work and Pensions, *LDCS* local data collection system (Public Health England), *LMS* Labour Market System (Department for Work and Pensions), *NDTMS* National Drug (and alcohol) Treatment Monitoring System, *ONS* Register deaths registered in England and Wales (Office for National Statistics), *OUD* opioid use disorder, *PIS/PCF* Participant Information Sheet/Participant Consent Form, *PNC* Police National Computer (Ministry of Justice), *p-NOMIS* National Offender Management Information System (Ministry of Justice), *R* randomisation, *RTI* Real Time Information database (Her Majesty’s Revenue and Customs), *SCID-5-CV* structured clinical interview for DSM-5 (alcohol and drug use) disorders, clinician version, *SHBE* Housing Benefit extract (Department for Work and Pensions), *STS* Staff Time Survey, *TAU* treatment as usual, *TOP* Treatment Outcomes Profile, *UCStats* Universal Credit Official Statistics (Department for Work and Pensions), *WPLS* Work and Pensions Longitudinal Study (Department for Work and Pensions), *UCFS* Universal Credit Full Service System Strategic Extract, Department for Work and Pensions, *UCStats* Universal Credit Official Statistics. All database names and acronyms are correct at the time of writing but may be subject to change and this will be noted in the analysis plans

### Sample size

Following preliminary planning, we followed the DELTA^2^ guideline to estimate the minimum sample size for the study [27]. Frederick and VanderWeele’s meta-analysis [7] was used to specify the important and realistic target difference for the primary outcome, with an estimate of its uncertainty. A sensitivity calculation was included if assumptions are mis-specified.

For comparison to the duration of the IPS intervention in IPS-AD, we used the rate of competitive employment status reported by seven superiority trials which evaluated 12 months of IPS (928 participants; outcome rate 0.36 for IPS and 0.13 for TAU; odds ratio (OR) 3.76; 95% CI 2.70 to 5.24). Conservatively, we used the lower bound of the CI (i.e. 2.70; equivalent to an outcome rate of IPS 0.36 and TAU 0.18).

To achieve 90% power to detect this 18% target difference (with a two-sided 5% level of statistical significance and a 20% increase to compensate for missing or inaccurate NINO information) we estimate that 302 participants will be required with AUD and OUD (giving an expected 95% CI estimate for the OR effect within a range from 1.50 to 4.36). If the observed effect falls short of the target difference, we will be able to detect a 15% difference (which we judge is still important) with 83% power (OR 95%, CI 1.24–3.46).

Given the lower number of people in treatment with other drug use disorders, we expect to recruit fewer participants in this group, so it will be realistic to power the analysis at 80%. For the 18% target difference (two-sided, 5% level of significance and with 20% increase for attrition), 228 participants will be needed (95% CI 1.35–4.57).

For the secondary outcome of total time worked, four of the seven trials used for the power calculation for the primary outcome measure in the meta-analysis reported the total number of hours worked (i.e. the sum of all time in all competitive employment during the trial). These four trials recruited 376 participants and the pooled mean difference was 505 h (Hedges’ *g* effect size = 0.54; 95% CI 0.33–0.74). Using this effect size as the realistic mean target difference, the analysis of the secondary outcome for length of competitive employment will have 99% to detect this target difference for the AUD and OUD groups. For the other drug use disorder group, we will be able to detect an effect size ranging from 0.54 to 0.38 with a minimum of 82% power.

With these conservative planning assumptions, a total of 832 participants will be the minimum number of participants required. Mediation analysis and longer-term follow-ups will benefit from a greater sample size, so recruitment is expected to extend well beyond this minimum.

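### The fallback power of 83%, the 82% for total time worked and the three expected confidence intervals ignore the loss that the sample size was inflated for

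*Protocol article*

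**What the plan says.** All the figures are in the Sample size section of the protocol article.

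- **Target effect.** The lower confidence bound from the meta-analysis, an odds ratio of 2.70, is taken as "equivalent to an outcome rate of IPS 0.36 and TAU 0.18".
- **AUD and OUD.** At 90% power, "we estimate that 302 participants will be required with AUD and OUD". This means 302 in each group, since 302 + 302 + 228 = 832. The number includes "a 20% increase to compensate for missing or inaccurate NINO information".
- **Expected precision.** The 302 is described as "giving an expected 95% CI estimate for the OR effect within a range from 1.50 to 4.36".
- **Fallback.** If the effect falls short of target, "we will be able to detect a 15% difference (which we judge is still important) with 83% power", with the interval given as "OR 95%, CI 1.24–3.46".
- **Other drug use disorder.** 228 participants at 80% power, again with a 20% increase, and an expected interval of 1.35–4.57.
- **Total time worked, other drug use disorder.** "we will be able to detect an effect size ranging from 0.54 to 0.38 with a minimum of 82% power".

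The section does not say that any of these figures assumes complete data on all 302 or 228.

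**The concern.** A sample size inflated for loss delivers its target power on the participants who remain after the loss. Any further power or precision figure attached to that sample should use the same remaining number. Here the headline powers use the number after loss, while the fallback power, the total-time power and the three intervals use the number before it. The same 20% serves once as a reserve against missing linkage and again as analysable data.

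The fallback is the plan's safeguard in case its assumptions are wrong, and it concerns a difference the authors still regard as important. A reader would conclude that each of the two larger groups keeps more than 80% power for that difference after the planned loss.

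A smaller question is whether an odds ratio of 2.70 matches the two rates said to be equivalent to it.

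**Working it through.** **Inputs.** Two-sided 5%; rates 0.36 and 0.18; power 90% and 80%; a 20% increase; effect size 0.38 (all from Sample size). Allocation is 1:1 (Procedure).

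**1. Headline sample sizes: these are after-loss figures.** With p̄ = (p₁ + p₂)/2,

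n per arm = [1.96·√(2p̄(1−p̄)) + z_power·√(p₁(1−p₁) + p₂(1−p₂))]² / (p₁ − p₂)²

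For 0.36 v 0.18 (p̄ = 0.27):

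- 90% power: 125.8, so 126 per arm, 252 in all; 252 × 1.2 = 302.4 (stated 302).
- 80% power: 94.3, so 95 per arm, 190 in all; 190 × 1.2 = 228 (stated 228).

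Power is 90.1% at 252 and 80.3% at 190. With no loss it would be 94.5% at 302 and 87.0% at 228.

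**2. Expected intervals: these are no-loss figures.** The interval is OR × exp(±1.96·SE), with SE = √(1/a + 1/(n−a) + 1/b + 1/(n−b)), on whole-number expected counts a and b out of n per arm.

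| Counts per arm | OR | SE | Interval | Stated |
|---|---|---|---|---|
| 54/151 v 27/151 | 2.557 | 0.272 | 1.50–4.36 | 1.50–4.36 |
| 54/151 v 32/151 | 2.070 | 0.262 | 1.24–3.46 | 1.24–3.46 |
| 41/114 v 21/114 | 2.487 | 0.311 | 1.35–4.57 | 1.35–4.57 |

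All three agree to two decimals with 151 and 114 per arm, that is, with all 302 and all 228. The second row also shows which rates lie behind the 15-point fallback: 0.36 v 0.21, which the section does not print.

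**3. Fallback power.** Inverting the formula in step 1:

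| Rates | 151 per arm (302) | 126 per arm (252) |
|---|---|---|
| 0.36 v 0.21 | 82.6% | 75.4% |
| 0.33 v 0.18 | 85.2% | 78.3% |

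For 0.36 v 0.21 the unpooled-variance version gives 83.3% and 76.3%. The stated 83% therefore reproduces at 302 and not at 252. Pooled, unpooled, arcsine, log-odds-ratio and exact chi-square calculations were tried for both pairs of rates; none reaches 80% at 252.

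**4. Total time worked.** Power = Φ(d·√(n/2) − 1.96):

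- 114 per arm: 0.38 × √57 = 2.869, power 81.8% (81.5% by noncentral t), which is the stated 82%.
- 95 per arm: 0.38 × √47.5 = 2.619, power 74.5% (74.1% by t).

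The same loss applies here. Total time comes from the employment database (Secondary outcome measures), and vocational outcomes are linked by National Insurance number (Information governance and data linkage).

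**5. Intervals after the planned loss.** With exact rates rather than rounded counts:

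- 0.36 v 0.18, 126 per arm: 1.43–4.59
- 0.36 v 0.21, 126 per arm: 1.21–3.71
- 0.36 v 0.18, 95 per arm: 1.31–5.01

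Rounding to whole counts shifts these limits somewhat; for example, 45/126 v 26/126 gives 1.22–3.76.

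**6. Odds ratio.** (0.36 × 0.82)/(0.64 × 0.18) = 0.2952/0.1152 = 2.56. An odds ratio of 2.70 with 0.36 on IPS gives TAU odds of 0.5625/2.70 = 0.2083, a rate of 0.2083/1.2083 = 0.172.

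**The case against.** The strongest reply is that no confirmatory result depends on these figures. They are per-disorder-group figures, the primary analysis pools all participants, and the analysis section calls the separate group models exploratory. Pooled, 252 + 252 + 190 = 694 evaluable participants give 99.3% power for 0.36 v 0.21. This is correct, and it limits the consequence. It does not make the printed figures right: the section justifies the sample size group by group, and its figures should hold on those terms.

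Second, the loss may be smaller than allowed for. Providing a National Insurance number is an inclusion criterion, linkage can fall back on name, date of birth and area of residence, and recruitment is expected to go well beyond 832. That is reasonable, but the stated figures are tied to 302 and 228, and those numbers exist because the plan allows for loss. If complete linkage is the basis, the headline powers should read 94.5% and 87.0%. No single basis gives both sets of figures.

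Third, the odds-ratio slip is conservative: a TAU rate of 0.18 rather than 0.172 asks for more participants, not fewer. This is also correct, so it is a wording error only.

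Finally, the plan speaks of a 20% increase and never of a 20% loss. Multiplying by 1.2 covers a loss of 16.7% (1 − 1/1.2). If a full 20% were lost, headline power would be 88.9% and 78.6% and fallback power about 74%. That is conditional on a loss rate the plan does not state, and the finding does not rely on it.

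**Conclusion.** The concern holds. Five figures are computed on the inflated sample while the headline powers beside them are computed after loss.

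| Figure | Stated | After the planned loss |
|---|---|---|
| Power, 15-point difference, AUD or OUD | 83% | 75–76% (0.36 v 0.21); 78–79% (0.33 v 0.18) |
| Power, effect size 0.38, other drug | 82% | 74% |
| Interval, 18 points, AUD or OUD | 1.50–4.36 | 1.43–4.59 |
| Interval, 15 points, AUD or OUD | 1.24–3.46 | 1.21–3.71 |
| Interval, 18 points, other drug | 1.35–4.57 | 1.31–5.01 |

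The two powers fall below 80%, which is the lower of the plan's own power targets. The intervals widen modestly and all still exclude 1.

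This rests on reading the 20% as the loss to be absorbed, which the 252-to-302 and 190-to-228 steps confirm, and on 0.36 v 0.21 as the fallback rates, which the stated interval confirms. The 832 total, the headline 90% and 80%, and the 99% for total time in AUD and OUD (99.0% at 252) are unaffected. The match between an odds ratio of 2.70 and 0.36 v 0.18 is inexact; the correct value is 2.56.

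**What to change.** In the Sample size section:

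1. Recompute the five figures at 252 and 190 evaluable participants, using the after-loss values above. Alternatively, keep the present values and state beside each that it assumes complete linkage of all 302 or 228.
2. Print the rates behind the 15-point fallback, 0.36 v 0.21.
3. Replace the claimed equivalence with a statement that 0.36 v 0.18 is an odds ratio of 2.56, just below the lower bound of 2.70.
4. Add a sentence that these are per-group figures and give the power of the pooled primary analysis after loss (about 99% for 15 points).

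The cost is a rewrite within one section, with some figures becoming less favourable. No extra participants and no design change are needed. Keeping the stated powers after loss would be a different choice: 83% for 0.36 v 0.21 needs about 306 analysed (306 × 1.2 ≈ 367 recruited) in each of AUD and OUD, and 82% for an effect size of 0.38 needs about 230 analysed (230 × 1.2 = 276 recruited) in the other-drug group.

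### The 83% and 82% power figures and the three expected confidence intervals count the loss allowance as analysed participants, while the 90% and 80% in the same section do not

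*Protocol article*

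**What the plan says.** All the figures are in the Sample size section of the protocol article.

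- The planning rates are "equivalent to an outcome rate of IPS 0.36 and TAU 0.18".
- The alcohol and opioid groups are each sized for 90% power at the 18-point difference, testing two-sided at 5%. The resulting number is then raised by "a 20% increase to compensate for missing or inaccurate NINO information". The outcome is 302 in each group, "giving an expected 95% CI estimate for the OR effect within a range from 1.50 to 4.36".
- As a sensitivity statement for those groups: "we will be able to detect a 15% difference (which we judge is still important) with 83% power (OR 95%, CI 1.24–3.46").
- The other-drug group is sized at 80% power with the same 20% addition, here described as being for attrition: "228 participants will be needed (95% CI 1.35–4.57").
- For time worked, the stated power is 99% in the alcohol and opioid groups at an effect size of 0.54. In the other-drug group, "we will be able to detect an effect size ranging from 0.54 to 0.38 with a minimum of 82% power".

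The section does not say which number of participants the sensitivity power, the time-worked powers or the intervals are computed on. It also does not give the two rates behind the 15-point difference.

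**The concern.** A sample size raised by 20% for loss carries its stated power on the number left after the loss. Any other power or expected interval quoted for the same design should use that number too, unless the text says otherwise. Here the added participants appear to be treated as lost for the headline powers and as analysed for the figures that follow.

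The 83% is the section's reassurance if the target difference proves too optimistic, and it refers to a difference the authors still regard as important. If it rests on participants whom the same section expects to lose, that reassurance is too strong for the analysis within one diagnosis group. The expected intervals are then too narrow for the same reason. Every discrepancy flatters the design.

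**Working it through.** **Inputs.** From the Sample size section: rates 0.36 and 0.18, two-sided 5%, power 90% and 80%, 20% increase, group sizes 302 and 228, effect size 0.38. From the Procedure section: allocation 1:1. Hence 151 and 114 per arm as recruited.

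**1. The headline sizes are net of loss.** Pooled-variance formula for two proportions, no continuity correction, with p̄ the mean of the two rates:

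n per arm = [1.96·√(2p̄(1−p̄)) + z_power·√(p1(1−p1) + p2(1−p2))]² / (p1−p2)²

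For 0.36 against 0.18, p̄ = 0.27:

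- 90%: (1.2306 + 0.7879)² / 0.18² = 125.75, so 126 per arm, 252 in total. 252 × 1.2 = 302.4, stated as 302.
- 80%: (1.2306 + 0.5174)² / 0.18² = 94.3, so 95 per arm, 190 in total. 190 × 1.2 = 228, as stated.

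The 90% and 80% therefore belong to 126 and 95 per arm. On 151 and 114 per arm the same formula gives 94.5% and 87.0%, which the section does not claim.

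**2. The stated intervals come from the inflated numbers.** Woolf interval: exp[ln OR ± 1.96·√(1/a + 1/(n−a) + 1/b + 1/(n−b))], with expected events rounded to whole numbers.

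| Comparison | Events | OR | SE of ln OR | 95% CI | Stated |
|---|---|---|---|---|---|
| 0.36 v 0.18, 151 per arm | 54 v 27 | 2.56 | 0.272 | 1.50–4.36 | 1.50–4.36 |
| 0.36 v 0.21, 151 per arm | 54 v 32 | 2.07 | 0.262 | 1.24–3.46 | 1.24–3.46 |
| 0.36 v 0.18, 114 per arm | 41 v 21 | 2.49 | 0.311 | 1.35–4.57 | 1.35–4.57 |

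All three match to two decimals. With the same rates at 126 or 95 per arm, none matches.

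**3. The stated powers come from the inflated numbers too.** For proportions, power = Φ{[(p1−p2)√n − 1.96·√(2p̄(1−p̄))] / √(p1(1−p1) + p2(1−p2))}. For 0.36 against 0.21:

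- 151 per arm: Φ(0.940) = 82.6% (stated 83%).
- 126 per arm: Φ(0.687) = 75.4%.

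For time worked at effect size d = 0.38, two-sample t-test with noncentrality d·√(n/2):

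- 114 per arm: noncentrality 2.87, power 81.5% (normal approximation 81.8%; stated 82%).
- 95 per arm: noncentrality 2.62, power 74.1% (normal approximation 74.5%). At 95 per arm, 82% is reached only at d of about 0.42.

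**4. Intervals on the analysable numbers.**

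| Comparison | Stated | Unrounded rates | Rounded events |
|---|---|---|---|
| 0.36 v 0.18, 126 per arm | 1.50–4.36 | 1.43–4.59 | 1.39–4.45 (45 v 23) |
| 0.36 v 0.21, 126 per arm | 1.24–3.46 | 1.21–3.71 | 1.21–3.76 (45 v 26) |
| 0.36 v 0.18, 95 per arm | 1.35–4.57 | 1.31–5.01 | 1.31–5.01 (34 v 17) |

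The unrounded version is preferable for restating, because rounding to whole events shifts the odds ratio itself (to 2.49 instead of 2.56 in the first row). The standard error grows by √1.2 = 1.095, about 10%.

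**5. Sensitivity to the inferred rates.** The pair 0.36 and 0.21 is back-solved. Other pairs 15 points apart give, at 126 per arm, 78% (0.33 v 0.18) and 76% (0.35 v 0.20). The pair 0.28 v 0.13 would give 84%, but its odds ratio of 2.60 does not fit the stated interval, whose centre is √(1.24 × 3.46) = 2.07.

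**6. Time worked, alcohol and opioid groups.** At d = 0.54, power is 99.7% at 151 per arm and 98.95% at 126. The stated 99% holds after the loss.

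**The case against.** The strongest reply concerns consequence. The primary analysis pools all participants in one mixed-effects logistic model (Primary vocational effectiveness), and the separate models by diagnosis are called exploratory. After the plan's own allowance about 832/1.2 = 693 participants remain, some 346 per arm. A simple test of 0.36 against 0.21 then has about 99% power, ignoring clustering by site. This stands, and it limits the point to the per-diagnosis figures. It does not make those figures right, since they are printed as properties of groups of 302 and 228.

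The loss may also be smaller than budgeted. Ability to supply a National Insurance number is an inclusion criterion, linkage can fall back on name, date of birth and postcode, and recruitment is expected to pass 832. So 75% is the value under the plan's own allowance, not a forecast. But the section uses that allowance to reach 302 and 228 and cannot drop it without saying so.

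Finally, the base and the 15-point rates are inferred. That is true of both. The inference is strong: three intervals and two powers agree with the inflated numbers. The 99% does not help to decide, because it is compatible with either base.

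**Conclusion.** The concern holds as an error in the printed figures. The Sample size section mixes two bases: 90% and 80% are net of the loss allowance, while the 83%, the 82% and the three expected intervals are gross of it. On the net numbers the 15-point power is about 75% (76–78% under the other plausible rate pairs). The other-drug power for time worked at 0.38 is about 74%, and the expected intervals rest on standard errors about 10% larger than those printed.

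This assumes the pooled-variance formula and Woolf interval, which reproduce the plan's own figures, and a loss that uses up exactly the 20% addition (one sixth of those recruited). If a full 20% of recruits were lost, leaving about 242 and 182, the two powers would be about 74% and 73% (normal approximation for the second), and the 90% and 80% would themselves fall to 88.9% and about 78.7%.

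The sizes of 302, 228 and 832, the 99% for time worked and the pooled primary analysis are not affected.

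**What to change.** Put every figure in the section on one base, and state the base and the rates.

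- Preferred: compute on 252 and 190. Give the 15-point power as 75%, naming the two rates assumed. Give the other-drug time-worked power at 0.38 as 74%, or the effect size detectable with 82% power as 0.42. Give the expected intervals as 1.43–4.59, 1.21–3.71 and 1.31–5.01.
- Alternative: keep the present figures, label them as applying if no participant is lost, and print the net figures beside them. The headline powers on that no-loss base would be 94% and 87%.

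In either case, say that these figures describe the analyses within a diagnosis group. The cost is wording only: no more participants and no change to the design or analysis, although some stated figures become less favourable.
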